### Secondary outcomes

#### Personality functioning

The Structural Clinical Interview for DSM-5 Personality disorders (SCID-5-P, [7]). This Dutch version of the SCID-5-P is used for diagnosing PDs at assessment and at 1-year follow-up. The SCID-5-P replaced the SCID-II. The exact reliability and validity of this version of the SCID-5-P is still unknown. Previous research, however, has shown adequate to good interrater reliability and test-retest interrater reliability of the original SCID-II, the Dutch version and translations of the SCID-5-P in other languages [42, 66, 71, 90]. Assessment using the SCID-5-P will be guided by items previously affirmed by the patient on SCID-5-PV (Structured Clinical Interview for DSM-5 Personality Questionnaire), a self-report questionnaire screening for PDs that will be completed at intake. Items not affirmed on the SCID-5-PV will be assumed to be true negatives; however, if a clinician has reason to believe these are false negatives, such items will be assessed. This method is in accordance with instructions for using the SCID-5-P and enables the assessment of PD symptoms to be based upon self-report combined with a structured clinical interview.Avoidant Personality Disorder Severity Index (AVPDSI) Dependent Personality Disorder Severity Index (DEPDSI), Compulsive Personality Disorder Severity Index (OCPDSI). These semi-structured interviews are developed to assess the frequency and severity of manifestations of the DSM-5 criteria of avoidant, dependent and compulsive PDs. For patients with a main diagnosis otherwise specified PD with predominantly Cluster-C traits, a personalized selection of the Cluster-C traits derived from the AVPDSI, DEPDSI and OCPDSI is made. These interviews have excellent interrater agreement (ICC>.90) and internal consistency (Cronbach *a*>.90) [44]. The interviews are modelled after the Borderline Personality Disorder Severity Index (BPDSI), measuring the severity of BPDs. The BPDSI is a reliable and valid instrument, suitable for use as an outcome measure [8, 43]. Total scores of the AVPDSI, DEPDSI and OCPDSI consist of a total sum of the average symptom scores per subsection of the interview, an average burden score and an average impact score. The scores on the instruments are converted into one severity score by standardizing the raw scores (see Groot et al. [44] for a description of the calculations per interview). To ensure quality of data collection of the AVPDSI, DEPDSI and OCPDSI, assessors will be trained, and all measurements will be audiotaped.Inventory of Personality Organisation Short Form (IPO-16-NL, [14]). The IPO-16-NL is the Dutch short version of the IPO-83 [21]. Norm scores of the German version are available and psychometric evaluation has shown good internal consistency, reliability, validity and confirmed a one factor structure of general personality dysfunction [107, 108]. The total score on the 16 items represents a dimensional measure of global severity of personality pathology according to Kernberg’s object-relationship framework.

#### Psychiatric symptoms

Brief Symptom Inventory (BSI, [26]). The BSI is a 53-item self-report instrument that will be used to measure general psychological distress. The answers are scored on a 5-point Likert scale. It is derived from the SCL-90-R and has demonstrated it to be an acceptable short alternative of its longer version [24].

#### Quality of life, happiness and psychosocial functioning

Quality of life (EQ-5D-5L, [48]). Quality of life is measured using the EQ-5D-5L. This self-report questionnaire assesses general quality of life using five domains: mobility, self-care, usual activities, pain/discomfort and anxiety/depression. Each dimension has 5 response levels: no/slight/moderate/severe/extreme problems. The Dutch norm scores will be used for calculating the mean EQ-5D utility values [99]. Psychometric study of the EQ-5D-5L has shown this version to be a valid and reliable extension of the three-level system [48, 52].Happiness Question [98]. The Happiness Question is added as a single question on general happiness in the months prior to the assessment and is scored on a 7-point Likert scale. This scale consists of the following verbal descriptions of different states of happiness: (1) completely unhappy, (2) very unhappy, (3) fairly unhappy, (4) neither happy nor unhappy, (5) fairly happy, (6) very happy, (7) completely happy. Dutch norms are available. For a single happiness item, high test-retest reliability (*r* = .86) and good concurrent, convergent, and divergent validity have been reported. The Happiness Question [28] has excellent sensitivity to change for patients with borderline PD who were treated with group ST.World Health Organization Disability Assessment Schedule (WHODAS 2.0, [95]). Psychosocial Functioning and Participation is administered with the WHODAS 2.0, a general measure of functioning and disability in major life domains, including understanding and communication, getting around, self-care, getting along with others, life activities and participation in society.

#### Costs

Treatment Inventory Cost in Psychiatric Patients (TiC-P, [97]). Societal costs are assessed using a specifically adapted version of the TiC-P. The TiC-P FORCE is a 14-item self-report questionnaire to assess health care costs (part I) and costs resulting from productivity losses (part II) associated with psychiatric disorders. In part I, the number of contacts with different health care providers over the last 6 months is assessed. Part II consists of items regarding absenteeism from paid and unpaid work and presenteeism (i.e. reduced productivity while at work) in the last 6 months.

#### Potential mediators

Potential mediators being measured are divided in potentially general working mechanisms and therapy-specific working mechanisms. For the general or common working mechanisms, the following instruments are selected:

Working Alliance inventory-short revised (WAI-SR). The WAI-SR is a 12-item self-report measure of the therapeutic alliance that assesses three key aspects of the therapeutic alliance: (a) agreement on the tasks of therapy, (b) agreement on the goals of therapy and (c) development of an affective bond. The WAI-SR demonstrated good psychometric properties [77].Difficult doctor-patient relationship questionnaire (DDPRQ-10, [45]). The DDPRQ-10 is a 10-item self-report questionnaire for therapists measuring the therapeutic relationship by investigating the extent to which patients are experienced as frustrating or difficult in the therapeutic relationship by their doctor or therapist. Five items are about the therapist’s subjective experience (e.g. “Do you find yourself secretly hoping that this patient does not return?”). Four items are quasi-objective questions about the patient’s behaviour (e.g. “How time consuming is care for this patient?”). One item combines elements of the patient’s behaviour and the therapist’s response (“To what extent are you frustrated by this patient’s vague complaints?”). The items are scored on a 6-point Likert scale. A high score reflects a high level of therapist frustration. In the study of Spinhoven et al. [91], the internal consistency of the DDPRQ-10 was .79.

In addition, instruments measuring potential working mechanisms specific to SPSP, APT and ST therapy are administrated in all three treatments.

For ST, the Schema Mode Inventory 2 (SMI-2, [12]) was selected to measure the schema modes:

For all three treatments, a self-report treatment integrity checklist is developed:I-FORCE Treatment Intervention List (I-FORCE-TIL)*.* After each therapy session, therapists will indicate which interventions they used in that session on a 30-item intervention list. This list has been developed by the authors of this study ([name] and [name], [109], internal publication), indicating the core interventions per treatment (SPSP, APT and ST) on a dichotomous scale (yes/no). Aim of this assessment is to register the applied treatment procedure. Reliability and validity checks will be performed on the I-FORCE-TIL.

#### Potential predictors and moderators

The selection of potential predictors or moderators to be examined was determined in consultation with experts:Inventory of Personality Organization (IPO-83-NL, [50]). The IPO is a self-report instrument consisting of 83 items on a 5-point Likert scale, based on Kernberg’s structural model of personality organization [21]. The Dutch version of the IPO has three main scales (Identity Diffusion, Primitive Defence and Reality Testing) and two supplementary scales (Aggression and Moral Values). The IPO-83-NL has good reliability and validity and appears to be a useful instrument to measure general personality pathology [15].Childhood Trauma Questionnaire-Short Form (CTQ-SF, [17]). This self-report measurement assesses childhood trauma. The short form was developed from the original 70-item version [16] and consists of 28 items measuring physical, sexual and emotional abuse and physical and emotional neglect. Its reliability and criterion-related validity have been established [17]. A recent study in the Netherlands confirmed its five-factor model [92].Nederlandse Narcisme Schaal (NNS, [34]). The NNS measures three dimensions of narcissism: overt (‘centrifugal’) narcissism and covert (‘centripetal’) narcissism and isolation. The questionnaire consists of 35 items with a 7-point Likert scale. Covert narcissism is hypothesized to be present in some patients with a Cluster-C PD and could possibly influence the outcome. The construction of this subscale is based on the Dutch translation of the hypersensitive narcissism scale [47] and consists of 11 items, with good reliability (Cronbach’s alpha .82). Dutch norms are available, although further research is necessary.Autism Spectrum Quotient short form (AQ-10). The AQ-10 Adult is derived from the original 50-item AQ [2], by a selection of the 10 items with the best discriminant validity. The questionnaire consists of 10 statements with for every statement four response options: strongly agree, slightly agree, slightly disagree, strongly disagree. At a cut-point of 6, sensitivity was .88, specificity was .91 and positive predictive value was .85.

#### Treatment retention

In case of dropout of treatment, the therapist completes a questionnaire that assesses the reasons for dropout. The research assistant invites the patient for an exit interview and motivates the patient for completing additional assessments that were scheduled at the beginning of treatment. Patients are considered early completers if both patient and therapist consider the treatment as being successful. Another possibility is a ‘push out’ of the treatment program for various reasons, e.g. if commitment problems persists, treatment has negative effects or if the safety of therapists is endangered in other ways.

### Participant timeline {13}

#### Sample size {14}^3^

First, the required sample size was calculated to compare the three types of active treatments. Three pairwise comparisons will be conducted between the active treatment arms (ST vs. APT, ST vs. SPSP; APT vs. SPSP). We want to detect a medium effect size (*f*=0.11) in a pairwise comparison of pre-post change between two active treatment arms, equivalent to *f*(*v*)=.2460 and Cohen’s *d*=.492, with Bonferroni-corrected *p* = 0.0167, a power of 0.80 and within-person correlation coefficient=0.60, for which 88 patients are needed per arm. Because three types of therapies will be compared, 3 × 88 = 264 participants are needed to perform three pairwise comparisons. We chose a medium effect size (f=0.11^4^) since this would also be a clinically meaningful difference, as opposed to a smaller effect size.

The correlation of 0.60 is an educated guess of the correlation between repeated assessments based on the previous RCTs the authors conducted.

The final analysis will be conducted with mixed regression on time series: the change in slope over time between two treatments. Because power analysis for mixed regression are complex and based on complex assumptions about the covariance-structure, a simplified approach was chosen by conducting a power analysis on the pre-post change.

**Fig. 1 Fig1:**
[figure not shown]
Flow chart of the study design

### Who will take informed consent? {26a}

The first screening for eligibility is done by the intake clinician when the patient enrols at the NPI. After a positive screening, the research assistants will obtain informed consent from the potential trial participants.

### Additional consent provisions for collection and use of participant data and biological specimens {26b}

Not applicable. The informed consent covers all necessary information.

## Assignment of interventions: allocation

### Sequence generation {16a}

When patients are eligible for participation, the informed consent is signed and the baseline assessment is completed, they will be randomized to SPSP, APT or ST by the independent statistician, using computerized random assignment.^5^ Randomization of patients will be pre-stratified according to type of PDs (avoidant, obsessive, dependent, otherwise specified PD) and location (Amsterdam or Amersfoort). According to the treatment capacity, the randomization rate between SPSP, APT and ST can be adjusted if necessary.

### Concealment mechanism {16b}

Allocation concealment will be ensured, as randomization is computer-generated and will only be done after the patient has signed the informed consent.

### Implementation {16c}

Allocation sequence will be done by an independent statistician with an 1:1:1 allocation, using a computer script performing block randomization. Enrolment and assignment will be done by the research assistants.

## Assignment of interventions: blinding

### Who will be blinded {17a}

Blinding of therapists and participants is not possible due to the nature of the study. The collection of treatment session recordings will include contact with therapists. The baseline assessments will be done by a research assistant blind for treatment allocation. The other assessments will be performed by independent research assistants blind to treatment. Blinding is done using password authorization for randomization.

### Procedure for unblinding if needed {17b}

Participants and therapists are not blinded; therefore, a procedure for unblinding is not applicable.

## Data collection and management^6^

### Plans for assessment and collection of outcomes {18a}

Data will be derived from electronic patient records and collected with an electronic Case Report Form (eCRF) using ACCESS. Patients will use an online survey (NetQ) to answer questionnaires. Interviews will be coded and results will be stored in NetQ. Audiotapes will be stored in MSTeams in a separate folder protected with a password. All data acquired during the study will be anonymized and saved in a study folder on our protected research server. Only the study team has access to this specific study folder.

### Plans to promote participant retention and complete follow-up {18b}

The patients will receive extensive information about the study set-up and requirements during the recruitment. The importance of completion of the follow-up will be stressed. Patients are allowed to stop at any time during the study and are not obliged to give a reason to discontinue. Questionnaires are completed using an online survey, and therefore patients can do this at any convenient moment plus minus 2 weeks from the assessment time-points. All patients are reminded throughout the study to fill out the questionnaires during study visits. Throughout the follow-up period, the researchers will check responses and if necessary contact patients for completion of their follow-up. Participants will receive a gift voucher of 20 euros after completing the assessment at 24 months and another 20 euros after the final follow-up measurement has been completed.

### Data management {19}

We use Case Report Forms (eCRF) in an online manner (digital platform NetQ), which will allow standardized data capture, as well as facilitate typing, versioning or uploading of documents. In addition, each assessment will have a standardized operational procedure (SOP) to increase internal consistency. Such SOPs determine who may conduct the assessment (either online or face-to-face), evaluation steps and standardized communication with research participants.

### Confidentiality {27}

Research data will be stored using a study identification code for each participant. The key of these numbers will only be available to the principal investigator and the independent statistician of Arkin Mental Health Care and will be documented and safeguarded by the principal investigator according to research guidelines after completion of the study. No patient identification details will be reported in publications.

### Plans for collection, laboratory evaluation and storage of biological specimens for genetic or molecular analysis in this trial/future use {33}

Not applicable, no biological specimens will be collected or analysed in this research.

## Statistical methods^7^

### Statistical methods for primary and secondary outcomes {20a}

#### Primary study parameter(s)

##### Treatment response: ADP-IV

All analyses will be conducted according to the intention-to-treat principle. Primary and secondary outcomes are analysed with Linear Mixed Models, with random effect of site (if estimation allows). The primary outcome measure is the change in the total ADP-IV score using the dimensional scoring algorithms [86]. Change in the primary outcome measure and the relative effectiveness of the three treatments will be analysed using mixed regression so that all available data are used, and taking into account the levels of participant and time. The addition of random levels for therapist, to adjust for possible therapist effects, will be tested. The underlying distribution of the mixed regression model will be determined based on the distribution of residuals (e.g. normal, gamma, negative binomial). Per-protocol analyses will also be conducted to test for robustness and sensitivity.

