**Methods:**

This is a mono-centre randomized clinical trial with three parallel groups: (1) SPSP, (2) APT, (3) ST. Randomization on patient level will be pre-stratified according to type of PD. The total study population to be included consists of 264 patients with Cluster-C PDs or other specified PD with mainly Cluster-C traits, aged 18–65 years, seeking treatment at NPI, a Dutch mental health care institute specialized in PDs. SPSP, APT and ST (50 sessions per treatment) are offered twice a week in sessions of 50 min for the first 4 to 5 months. After that, session frequency decreases to once a week. All treatments have a maximum duration of 1 year. Change in the severity of the PD (ADP-IV) will be the primary outcome measure. Secondary outcome measures are personality functioning, psychiatric symptoms and quality of life. Several potential mediators, predictors and moderators of outcome are also assessed. The effectiveness study is complemented with a cost-effectiveness/utility study, using both clinical effects and quality-adjusted life-years, and primarily based on a societal approach. Assessments will take place at baseline, start of treatment and at 1, 3, 6, 9, 12, 18, 24 and 36 months.

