#### Secondary study parameter(s)

##### (Differential) treatment response: secondary study parameters

We will examine change in the secondary outcome measures in the three treatments using mixed regression analysis. The secondary outcome measures include diagnostic status, reliable change and recovery, personality functioning, general functioning, general psychopathology, quality of life and happiness. As the PD severity indices AVPDSI, DPDSI and OCPDS vary per primary PD, they will be first standardized before they are analysed in the complete sample. This analysis will be controlled for primary PS, to account for possible differences in sensitivity to change. The underlying distribution of the mixed regression model will be determined based on the variable type (scale, nominal) and the distribution of residuals (e.g. normal, gamma, negative binomial). In addition, preliminary analyses will test differential treatment retention using survival analysis and mixed logistic regression. Medication confounds will be examined.

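### Randomisation is stratified by PD type and location, but the described primary model names no PD-type term and makes site an optional random effect; if the strata predict change in ADP-IV, some precision is forgone

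*Protocol article*

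**What the plan says.** Under Sequence generation {16a}: "Randomization of patients will be pre-stratified according to type of PDs (avoidant, obsessive, dependent, otherwise specified PD) and location (Amsterdam or Amersfoort"). Under Implementation {16c}: "Allocation sequence will be done by an independent statistician with an 1:1:1 allocation, using a computer script performing block randomization". The abstract mentions only the first factor: "Randomization on patient level will be pre-stratified according to type of PD".

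Under Treatment response: ADP-IV, the analysis is described as "Primary and secondary outcomes are analysed with Linear Mixed Models, with random effect of site (if estimation allows"), using "mixed regression so that all available data are used, and taking into account the levels of participant and time". A therapist level is to be tested. No term for PD type is named there.

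PD type does appear elsewhere. It is listed among the general potential predictors (Potential predictors) and as a subgroup factor (Methods for additional analyses {20b}). For the standardised PD severity indices, the secondary analysis section says: "This analysis will be controlled for primary PS, to account for possible differences in sensitivity to change". I read PS there as PD.

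The treatment comparison is a slope comparison. Sample size {14} states: "The final analysis will be conducted with mixed regression on time series: the change in slope over time between two treatments".

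**The concern.** Stratified blocks make the arms more alike on PD type and location than simple randomisation would. If those factors also predict the outcome, the true sampling variance of the treatment contrast shrinks. A model without them does not see this. It leaves the between-stratum variance in the residual, reports standard errors that are too large, and tests below its nominal level.

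Two features make this more than silence about covariates.

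- **Location gets an explicit but fragile place in the model.** The stratification uses two locations, and Study setting {9} lists four (three in Amsterdam, one in Amersfoort). A between-site variance then rests on 1 or 3 degrees of freedom. It can easily be estimated at zero, and the conditional wording then allows the term to be removed. Whether a design factor stays in the primary analysis would depend on the data.
- **The article names PD type when it intends to control for it.** It does so for the severity indices, on the ground that disorders may differ in how much they change. Change over time is also what the primary contrast measures.

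At stake is precision that could be had at almost no cost. The sample size has little slack and, as Limitations concedes, no allowance for dropout.

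**Working it through.** **Inputs from Sample size {14}.** f = 0.11, within-person correlation 0.60, d = 0.492, Bonferroni-corrected level 0.0167, power 0.80, 88 per arm.

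**Assumptions.**
- R², the share of variance in ADP-IV change explained by PD type and location, is not in the documents. I use 0 to 0.15.
- The test is two-sided. The article does not say so, but its figure reproduces that way.
- Allocation is 1:1:1 within strata. Sequence generation {16a} lets the ratio be adjusted to capacity, which is not modelled here.

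**Step 1: the plan's own figure.** f(V) = 0.11 × √(2/(1 − 0.60)) = 0.2460, and d = 2 × 0.2460 = 0.492. The normal approximation gives 87 per arm. The exact noncentral F gives power 0.7952 at 87 and 0.8005 at 88, so 88 is confirmed. A one-sided test would give 73. The calculation contains no covariates, so it does not depend on the strata.

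**Step 2: analysis with and without the strata.** Let δ = 0.492 × √(88/2) = 3.264 and z = z(1 − 0.0167/2) = 2.393.

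- Model SE, unadjusted relative to adjusted: 1/√(1 − R²)
- Power, adjusted: Φ(δ/√(1 − R²) − z)
- Power, unadjusted after stratified allocation: Φ((δ − z)/√(1 − R²))
- Actual level, unadjusted: 2 × [1 − Φ(z/√(1 − R²))]

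The unadjusted formula differs from the planned-power formula because stratified allocation has already reduced the true variance, while the reported SE has not followed.

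| R² (assumed) | SE too large by | Power unadjusted | Power adjusted | Gain (points) | Actual level (nominal 0.0167) |
|---|---|---|---|---|---|
| 0 | 0% | 80.8% | 80.8% | 0 | 0.0167 |
| 0.02 | 1.0% | 81.0% | 81.7% | 0.7 | 0.0156 |
| 0.05 | 2.6% | 81.4% | 83.0% | 1.6 | 0.0141 |
| 0.10 | 5.4% | 82.0% | 85.2% | 3.2 | 0.0117 |
| 0.15 | 8.5% | 82.7% | 87.4% | 4.7 | 0.0094 |

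Example at R² = 0.10, where √0.90 = 0.9487: adjusted, 3.264/0.9487 − 2.393 = 1.047 and Φ = 0.852; unadjusted, 0.870/0.9487 = 0.917 and Φ = 0.820.

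**Step 3: simulation.** Individual slopes were generated under stratified blocks, 4,000 runs per setting. At R² = 0.10 the unadjusted model SE averaged 0.118 against an empirical SE of 0.111 to 0.112. Rejection under the null was 0.012, and power was 81.0% unadjusted against 84.5% adjusted. At R² = 0 power was 79.5% against 79.3%, so there was no loss.

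**Step 4: which terms help a slope contrast.** Mixed models with random intercept and slope were fitted to 15 simulated data sets. The mean SE of treatment × time was:

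- no strata: 0.1243
- PD type and location as main effects only: 0.1243
- main effects plus interactions with time: 0.1229, about 1% lower

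The participant intercept already absorbs stratum differences in level, so only the interactions with time reach the slope. The 1% agrees with the formula. The simulated PD-type slope offsets (0.15, −0.15, 0.075, −0.075 with shares 45%, 20%, 10%, 25%) have variance 0.016. Total variance of an individual slope is 0.40² + 0.016 + 0.63²/0.770 = 0.69, where 0.770 is the sum of squared deviations of the visit times 0, 1, 3, 6, 9 and 12 months in years. So R² is about 0.023, and 1/√(1 − 0.023) = 1.012.

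**The case against.** The strongest reply is that the article does not exclude PD type. Its primary-analysis paragraph mainly describes random structure and gives no full list of fixed effects. Medication, which the section on concomitant care {11d} says will be analysed as a running covariate, is not mentioned there either. The text is condensed and calls its own methods provisional, and a full covariate list may sit in an analysis plan not shown. This stands as a limit: a reader might infer that the plan rejects adjustment for PD type, and the document does not say that. It does not remove the point about location, where the article makes a choice, and that choice lets a design factor drop out.

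A second reply is that the adjustment of the severity indices proves little about ADP-IV. Those interviews differ by primary disorder and must be standardised, whereas ADP-IV is one questionnaire for everyone. That is fair. The passage shows that the authors think differential change possible, not that it occurs on the primary outcome.

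A third reply is that any error is conservative and small. That also stands. A reader might infer that power falls below plan, or measure the gain against a fixed 80%. Neither is supported: 88 per arm assumed no covariates, and unadjusted power itself rises slightly under stratified allocation. Nor do the documents support a claim of bias or of an inflated type I error.

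Finally, the abstract naming only PD type could be read as a contradiction. It is better read as abbreviation, since the randomisation section gives both factors.

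**Conclusion.** The point holds as a conditional, minor efficiency issue. Both factors stratify the randomisation; the described primary model names no PD-type term and ties location to a variance component that may not be estimable. If the strata predict change in ADP-IV, reported standard errors are too large by about 2.6% to 8.5% for R² of 5% to 15%, the test is conservative, and 1.6 to 4.7 points of power are forgone. With R² of 2% the gain is 0.7 points, and with R² of zero there is none. The size rests wholly on the assumed R², and on near-equal allocation within strata. That PD type is absent from the model is partly an inference from a condensed and provisional text; that site is conditional is stated outright.

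**What to change.** In Treatment response: ADP-IV, replace the optional random effect of site with fixed effects for PD type (four levels) and location (Amsterdam or Amersfoort), each with its interaction with time, and state that these terms are kept whatever the data show. The interactions are essential, because main effects alone leave the slope SE unchanged. The therapist level can be handled as already planned.

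The cost is one sentence. Both factors are known at randomisation. With time entered linearly there are 3 + 1 = 4 main effects and 4 interactions, so 8 parameters in 264 patients; coding time as categories would add more. The sample size need not change.

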### Objectives {7}

The primary aim of this study is to compare the effectiveness and cost-effectiveness of the three individual treatments (SPSP, APT and ST) for Cluster-C PDs. The primary outcome of this superiority study is the severity of Cluster-C PD. We will compare the slopes over time of the three treatments from 0 to 12 months, with assessments of Cluster-C PD severity taking place at baseline, 1, 3, 6 and 9 months. Additionally, we will research differences between the outcomes of the three treatments at 18, 24 and 36 months follow-up. No hypothesis was formulated about the direction of a difference.

The second aim of this study is to explore working mechanisms by focussing on therapy-specific factors in the context of the contribution of common factors across psychotherapies. Selected therapy-specific factors are as follows: therapy-specific interventions; insight for SPSP; change in affect, defence style, perception of the self for APT; change in schema modes for ST. Working alliance is the non-specific factor being investigated.

The third aim is to identify general and specific predictors. Potential moderators will be studied exploratively. Firstly, we hypothesize that patients with relatively more childhood trauma will benefit more from ST than SPSP and APT, because of the use of imaginary rescripting, an evidence-based trauma processing technique [35, 83]. Secondly, we expect that patients with more severe personality pathology (e.g. borderline personality organization (Kernberg, [57]) will profit more from ST or SPSP than APT. This is because these therapies are developed and have proven their effectiveness for a broader range of PDs [60, 88], whereas APT is originally designed for the Cluster-C/neurotic population [25].

The relationship between specific treatment interventions, mediators and outcome will also be explored. Therapists will indicate per session which of the core interventions per treatment they have applied in their sessions. The hypothesis is that certain interventions will be stronger connected to mediators and outcome than others. For example, experiential techniques (imagery rescripting, multiple chair technique) for ST; adequate support for SPSP; facilitation of expression of emotions for APT.

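### The primary comparison is a change or slope in ADP-IV from baseline with no baseline adjustment specified; fixing a common baseline mean would gain precision at no cost in data

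*Protocol article*

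**What the plan says.** Under Treatment response: ADP-IV, the article says "The primary outcome measure is the change in the total ADP-IV score using the dimensional scoring algorithms". It names linear mixed models with participant and time levels, a random site effect if it can be estimated, and a therapist level to be tested. It does not write out the fixed effects.

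Under Objectives {7}: "We will compare the slopes over time of the three treatments from 0 to 12 months, with assessments of Cluster-C PD severity taking place at". The times listed there are month 0 and months 1, 3, 6 and 9. The abstract also lists month 12. Baseline is therefore one of the points that define the slope.

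Under Sample size {14}, the final analysis is the difference in slope between two treatments, but "a simplified approach was chosen by conducting a power analysis on the pre-post change". The inputs are f = 0.11, "equivalent to *f*(*v*)=.2460 and Cohen’s *d*=.492, with Bonferroni-corrected *p* = 0.0167", and "a power of 0.80 and within-person correlation coefficient=0.60, for which 88 patients are needed per arm".

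Under Sequence generation {16a}, once "the informed consent is signed and the baseline assessment is completed, they will be randomized". Strata are type of personality disorder and location, not ADP-IV severity.

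No section names baseline ADP-IV as a covariate or says whether the arms share a baseline mean. The section on concomitant care does name medication and co-interventions as covariates.

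**The concern.** Because baseline is measured before randomisation, the true arm means are equal at that point. A model that estimates a separate baseline mean for each arm ignores this. With two time points, an arm, time and arm-by-time model with free baseline means is exactly a change-score comparison. A model with one common baseline mean is, in effect, analysis of covariance and has smaller variance whenever the correlation is below 1.

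At stake is the precision of all three pairwise tests at 0.0167. The Limitations section says that the sample size was not raised for dropout and relies on the mixed model to make up for it, so spare precision is worth having.

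**Working it through.** **Inputs.** All from Sample size {14}: f = 0.11, correlation ρ = 0.60, alpha 0.0167 (two-sided, as no direction is hypothesised), power 0.80, 88 per arm. Power below is from the noncentral t distribution with 174 df.

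**1. The protocol's own figure.**
- f(V) = √(f² × 2 / (1 − ρ)) = √(0.0121 × 2 / 0.40) = 0.246, so d = 2 × 0.246 = 0.492. Both match.
- Power is 0.795 at 87 per arm and 0.800 at 88. The stated 88 reproduces.

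**2. The same difference with baseline adjustment, pre-post.** In units of the baseline SD:
- Variance of change: 2(1 − ρ) = 0.80.
- Raw difference: 0.492 × √0.80 = 0.44 SD.
- Variance after baseline adjustment: 1 − ρ² = 1 − 0.36 = 0.64, a fall of 20%.
- Standardised difference: 0.44 / √0.64 = 0.55.
- Standard error: √(2 × 0.80 / 88) = 0.135 for change, √(2 × 0.64 / 88) = 0.121 adjusted.
- Power: **0.800 for change, 0.890 adjusted**. With adjustment, 71 per arm would give 80%.

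**3. Sensitivity to the correlation.** The article calls 0.60 a guess: "The correlation of 0.60 is an educated guess of the correlation between repeated assessments". Holding the raw difference at 0.44 SD:

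| ρ | Change | Adjusted | Gain (points) |
|---|---|---|---|
| 0.5 | 0.692 | 0.829 | 14 |
| 0.6 | 0.800 | 0.890 | 9 |
| 0.7 | 0.910 | 0.952 | 4 |

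**4. The planned contrast: a linear slope over several visits.** Generalised least squares, 88 per arm, 0.44 SD difference at month 12, no dropout. The covariance structures are my assumptions, since the article gives none. The random-slope case has intercept variance 0.7, residual variance 0.3 and slope SD 0.05 per month, uncorrelated; this gives a correlation of 0.60 between months 0 and 12.

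| Visits (months) | Covariance | Free baseline | Common baseline | Gain (points) |
|---|---|---|---|---|
| 0, 1, 3, 6, 9, 12 | Compound symmetry, 0.60 | 0.948 | 0.971 | 2 |
| 0, 1, 3, 6, 9, 12 | Decaying to 0.60 at month 12 | 0.800 | 0.890 | 9 |
| 0, 1, 3, 6, 9, 12 | Random intercept and slope | 0.829 | 0.848 | 2 |
| 0, 1, 3, 6, 9 | Compound symmetry, 0.60 | 0.666 | 0.739 | 7 |
| 0, 1, 3, 6, 9 | Decaying to 0.60 at month 12 | 0.628 | 0.717 | 9 |

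With a larger random-slope SD (0.10 per month, visits to month 12) the gain falls to under 1 point. It is not negative in any structure tried.

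**5. Baseline as a covariate on post-baseline scores.** If the slope contrast is kept, this removes month 0 from the slope. Under compound symmetry at 0.60, power falls from 0.948 to 0.839 (visits to month 12) and from 0.666 to about 0.47 (visits to month 9). The two forms of adjustment are not interchangeable for a slope.

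**The case against.** The strongest reply is that the article never says the model is unadjusted. It lists no fixed effects, a change or slope outcome is compatible with a common-baseline model, and the statistical section closes by calling its methods provisional. Baseline parameterisation is often left to an analysis plan, which is not shown here. The sample-size section separates the simplified pre-post calculation from the final mixed model, so the former does not define the latter. This stands. A reader might infer that an unadjusted analysis has been chosen; the text supports only that no adjustment is specified.

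A reader might also infer that the trial loses 9 points of power or is underpowered. That does not follow either. The 9 points belong to the two-time-point simplification, and the pre-post design reaches its 80% without adjustment.

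Nor does chance baseline imbalance bias the change contrast: under randomisation it is unbiased, and the imbalance is already counted in the variance of 0.80 against 0.64.

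What the objection does not remove is that the article's three descriptions of the primary comparison all rest on change from baseline, that it addresses other adjustments, and that it leaves out the one variable whose benefit follows from its own inputs.

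**Conclusion.** The point holds as an efficiency gain that the protocol has not secured. On its own pre-post inputs, baseline adjustment takes power from 80% to about 89%. For the planned slope analysis the gain is roughly 0 to 9 points, depending on the covariance and the visits used. The figures assume ρ = 0.60, a 0.44 SD difference at month 12, a linear trend, full data and, for the slope model, the structures listed. They describe what a free-baseline model would forgo; whether the final model would be of that kind cannot be told from the article. The improvement is worth making because it needs only data already collected, and because settling the baseline handling beforehand removes a choice that could otherwise be made after the data are seen.

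**What to change.** In the primary-outcome paragraph of the statistical methods, state that the mixed model gives all arms a common baseline mean: no arm effect at time 0, with arm entering only through arm-by-time terms. Apply the same rule to the secondary outcomes measured at baseline. Report the free-baseline model as a sensitivity analysis.

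Use baseline ADP-IV as a covariate on post-baseline scores only if the contrast is an adjusted level difference, for example at month 12, and not a slope with month 0 removed.

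Keep the 264 patients. The cost is a sentence or two of model wording, with no new data.
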